This is an abridged translation of the original document which was written in Japanese.

## **1. Key decision criteria and multiplicity adjustment**

### **1.1. Key decision criteria for study results**

The purpose is to test whether one of the two deemed standard-of-care arms A (EP-therapy) and B (IP-therapy) outperforms the rest regarding the primary endpoint, overall survival.

We conclude that EP therapy is a more useful treatment when the two-sided p-value is less than 10% and the survival curve of EP therapy exceeds that of IP therapy. Meanwhile, we conclude that IP therapy is a more useful treatment when the two-sided p-value is less than 10% and the survival curve of IP therapy exceeds that of EP therapy. If the difference was not significant at a two-sided significance level of 10%, one of the two deemed standard treatment cannot be judged to be more useful. In this case, we conclude that both regimen continue to be the standard of care, as there is no evidence to actively recommend either one of them.

### **1.2. Multiplicity Adjustment**

For a reason that our primary interest is whether either of two arms is superior to the other, two-sided test is used. The study-wise significance level is set at two-sided 10%. In the primary analysis, two-sided 90% confidence intervals corresponding to a two-sided 10% significance level will be calculated, and in the other analyses, two-sided 95% confidence intervals will be calculated for descriptive purposes.

Significance levels and corresponding confidence coefficients used to test the primary hypotheses are based on the multiplicity adjustment associated with the interim analysis.

## **2. Efficacy analysis**

### **2.1. Analyses of primary endpoint**

#### **2.1.1. Primary analysis methods**

The primary analysis will be the final analysis unless this study is withdrawn from the interim analysis. In the primary analysis, the null hypothesis of equality of the overall survival among the two groups will be tested by stratified log-rank test. The stratification factors include randomization adjustment factors except institution (i.e., primary organ [gastrointestinal vs. hepatobiliary-pancreatic]) in all enrolled patients. However, if it is assumed that a stratified log-rank test cannot be performed appropriately, such as when the number of subjects and events in each stratum is small, handling of randomization adjustment factors will be addressed in the statistical analysis plan which will be finalized without information related to the comparison between groups before performing a confirmatory analysis.

Cumulative survival curves, median survival times, and annual survival rates are estimated using Kaplan-Meier method. Brookmeyer and Crowley methods are used to obtain 95% confidence intervals for median survival. Greenwood's formula is used to obtain 95% confidence intervals for annual survival rates. If the required number of events has been reached at 1 year after completion of enrollment, the final analysis will be performed at 1 year after completion of enrollment. Conversely, if the required number of events is not reached, follow-up will continue until the required number of events is reached to ensure power, and the final analysis will be performed without waiting for the end of the remaining follow-up period when the required number of events is found to be reached within the follow-up period. The final analysis will be summarized by the Data Center as the "Final Analysis Report" and submitted to the Research Secretariat, Research Representatives, Group Representatives, Group Secretariats, Data and Safety Monitoring Committee, and JCOG Representatives.

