#### **2.1.2. Analysis methods using statistical models**

As a treatment effect measure, hazard ratios and their confidence intervals for treatment effects between groups are estimated using stratified Cox proportional hazards models with the same factors as the stratified log-rank test for the primary analysis.

To investigate the interaction between treatment effect and the subpopulation, hazard ratios and their 95% confidence intervals for treatment effects will be calculated using unstratified Cox's proportional hazards model. These will be done in an exploratory manner with respect to the following factors. Because these analyses are not adequately powered and do not adjust for multiplicity, the results of each subgroup analysis should be interpreted as exploratory.

Factors planned for subgroup analysis:

- PS0/1
- Age 65 years or older/<
- Gender (male/female)
- Primary organ (gastrointestinal tract/hepatobiliary pancreas)
- Organ of origin (esophagus/stomach/small intestine/large intestine/pancreas/biliary tract/liver NEC (liver primary or liver metastasis of unknown primary))
- Organ of origin (pancreas/non-pancreas)
- Extent of extension of the primary lesion (locally advanced/distant metastasis or recurrence)
- Extent of extension of the primary lesion (locally advanced/distant metastasis/recurrence)
- Prior radical resection of the primary lesion (none/present)
- Pathological diagnosis was biopsy/resection specimen
- Grade 3 tumour with morphologically similar features of NETs but Grade 3 proliferative activity/morphologically more atypical (previously classified as poorly differentiated endocrine carcinoma) on histopathology with central pathology
- Histopathological examination by central pathological diagnosis, including Small cell carcinoma/Large cell carcinoma /
- Histopathologically diagnosed by central pathology, Ki67 50% or higher/less than 50%

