## 7. Planned accrual, accrual period, and follow-up periods

As described in "Section 2.4.2. in the protocol. Based on the background presented in Clinical Hypothesis and Rationale for Number of Enrollment", we assume a median survival of 8 and 12 months (HR=0.67) for inferior and superior treatment groups. Total of 63 patients per group and 126 patients in both groups (114 events required) will be required using the method of Schoenfeld and Richter. The above calculation assumes 6 years of enrollment, 1 year of follow-up,  $\alpha = 10\%$  (two-sided), and 70% power. The required number of patients and events are listed in table below when median survival time of arm A is different to the expectation.

Table: Number of Analyses Required (Number of Events Required)

| Median Survival
(mo) | Power    |          |          |          |
|-------------------------|----------|----------|----------|----------|
|                         | 65%      | 70%      | 75%      | 80%      |
| 7.0 vs. 10.5            | 108(100) | 124(114) | 142(131) | 162(150) |
| 8.0 vs. 12.0            | 112(100) | 126(114) | 144(131) | 166(150) |
| 9.0 vs. 13.5            | 114(100) | 130(114) | 148(131) | 170(150) |

※ Number of required events in parentheses

Based on these, the following will be established in view of some cases of loss to follow-up.

Planned enrollment: 70 patients in each group and 140 patients in both groups

Enrollment period: 6 years, follow-up period: 1 year after completion of enrollment

Consider sample size recalculation (SSR) if the prognosis is obviously better than assumed, or if 70 or more patients are enrolled within first 2.5 years. The SSR needs reconsideration of clinically meaningful differences in a blinded fashion and needs to be performed prior to the conduct of the primary analysis.

<Additions in protocol ver. 1.1>

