The registration pace after the enrollment start was smooth and exceeded the plan, and 70 cases were enrolled in October, 2016, when 2 years and 2 months passed from the enrollment start, which met the above-mentioned criteria for SSR. SSR with an aim of raising power to 80% was accepted at the meeting of the Hepatobiliary and Pancreatic Group on October 29, 2016, the group meeting of the Esophageal Cancer Group on November 19, 2016, and the group meeting of the Gastric Cancer Group on January 7, 2017. Therefore, the required number of enrollment was changed to 170. In addition, the "1-year analysis period" was added to the study period, and the following changes were made.

Planned enrollment: 85 patients in each group and 170 patients in both groups

Enrollment period: 6 years;

Follow-up period: 1 year after completion of enrollment;

Analysis period: 1 year;

Total study period: 8 years

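### The primary OS test and hazard ratio are valid with primary organ as the only stratum, but they forgo power that pre-specified adjustment for performance status would give if PS is strongly prognostic

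*SAP*

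**What the plan says.** Section 2.1.1 tests OS in all enrolled patients with a stratified log-rank test. On the strata it says: "The stratification factors include randomization adjustment factors except institution (i.e., primary organ [gastrointestinal vs. hepatobiliary-pancreatic". The supplemental note for the final analysis (2021/6) confirms this factor after finding enough deaths in each stratum. Section 2.1.2 estimates the hazard ratio "using stratified Cox proportional hazards models with the same factors as the stratified log-rank test for the primary analysis".

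PS 0/1 appears in the exploratory subgroup lists for OS, PFS and response. For OS, covariate adjustment appears only in 2.1.3, as a sensitivity analysis to be run if needed and limited to factors that turn out unbalanced between arms. PS is not named there, so no OS analysis is certain to adjust for it.

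On power, Section 7 states: "we assume a median survival of 8 and 12 months (HR=0.67) for inferior and superior treatment groups". After the sample size recalculation it adds: "SSR with an aim of raising power to 80% was accepted". Section 1.2 sets the error rate: "The study-wise significance level is set at two-sided 10" percent.

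**The concern.** With a hazard ratio, leaving out a prognostic baseline factor has a cost even when the arms are balanced on it. If the treatment effect is a constant HR within levels of the factor, the unadjusted HR moves towards 1 and the log-rank test loses power. Type I error is unaffected.

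This matters here for two reasons. Enrolment was raised from 140 to 170 to lift power from 70% to 80%, so an avoidable loss would undo part of that gain. And under Section 1.1 a non-significant result is itself a conclusion, namely that both regimens stay standard, so lost power feeds straight into the trial's decision.

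**Working it through.** **Inputs from the SAP.** Two-sided alpha 10%; medians 8 and 12 months (HR 2/3); "Planned enrollment: 85 patients in each group and 170 patients in both groups"; "Enrollment period: 6 years" plus 1 year of follow-up; final boundary |Z| > 1.6487 (two-sided 0.0992).

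**Step 1: the plan's own figure.** By Schoenfeld, events = 4(z₀.₉₅ + z_power)² / (ln HR)². With HR = 2/3 and power 65/70/75/80% this gives 100.3, 114.5, 130.9 and 150.4. The SAP table row for 8 vs 12 months reads "112(100) | 126(114) | 144(131) | 166(150", with events in parentheses, so the event counts reproduce. Power at 150 events is 79.9%. At 151 events and the final boundary it is 80.0%. The formula takes one overall HR and needs no PS adjustment.

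**Step 2: are the plan's medians compatible with a loss?** Let survival be exponential within each PS level, with HR 2/3 within levels. Every hazard in the superior arm is then 2/3 of its counterpart, so S_sup(t) = S_inf(2t/3) for the whole arm. The whole-arm median becomes 8 × 3/2 = 12 months whatever the PS effect. A loss can therefore arise with the stated medians met, although the whole-arm HR is then no longer a constant 2/3.

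**Step 3: organ-only against four organ × PS strata.** Assumptions not in the SAP: PS HR 1 to 3, PS 1 in 30% or 50%, organ split 50:50 without prognostic effect, exponential survival, no loss to follow-up, interim crossing ignored. Simulation of 170 patients, uniform accrual over 72 months, cutoff at the 150th death, 10,000 runs per setting. Power (%):

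| PS HR | 30% PS 1: organ | 30%: organ × PS | 50% PS 1: organ | 50%: organ × PS |
|---|---|---|---|---|
| 1.0 | 77.2 | 75.7 | 77.6 | 76.0 |
| 1.5 | 77.0 | 77.3 | 75.9 | 76.6 |
| 2.0 | 73.5 | 76.3 | 71.8 | 76.2 |
| 2.5 | 71.2 | 76.6 | 69.3 | 77.1 |
| 3.0 | 68.7 | 77.0 | 64.6 | 76.2 |

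The value near 77% with no PS effect is unrelated to PS. It reflects the Schoenfeld approximation when most patients have died, together with the final boundary. With the cutoff at 84 months instead (about 151 to 155 deaths), organ-only power at PS HR 1.0 is 79.6%.

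**Step 4: what four strata cost when PS is weak.** With the 84-month cutoff and 8,000 runs, organ-only against organ × PS gives 79.6% vs 78.0–78.2% at PS HR 1.0, 78.9–79.0% vs 78.2–78.3% at 1.25, and 77.8–78.2% vs 78.2–78.5% at 1.5. Four strata lose about 1.5 points if PS is not prognostic.

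**Step 5: PS as a covariate in the organ-stratified Cox model (score test).** Same 84-month design:

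| PS HR | Organ-only log-rank | Organ-stratified Cox with PS |
|---|---|---|
| 1.0 | 80% | 80% |
| 2.0 | 73–75% | about 79% |
| 2.5 | 69–72% | 78–80% |

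**Step 6: error rate and estimate.** Null rejection of the organ-only test was 10.0 to 10.3%, and it stays near 10% with PS adjustment. At PS HR 2.0 to 2.5 the organ-only HR lies about 2 to 5% nearer 1: 0.667 × 1.02 = 0.68 to 0.667 × 1.05 = 0.70.

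**The case against.** The strongest reply is that the SAP contains no error here. Stratifying by the randomization factors other than institution is a coherent rule. On this text PS is not one of those factors, so the rule leaves nothing out. This stands.

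A reader might infer that power falls below 80% as soon as PS is prognostic. The documents do not support that. The 80% is a Schoenfeld figure for an overall HR of 0.67. If 0.67 is the overall proportional HR, the organ-only test keeps its formula power and PS adjustment only adds to it. The loss needs the further assumption that 0.67 applies within PS levels.

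The driver also lies outside the document. The SAP nowhere says that PS is prognostic, how strongly, or how common PS 1 is, and a place in a list of exploratory subgroups is no evidence of it. The same argument could be made for other listed factors. This stands as a limit on the size of the gain. It does not remove the case for settling the choice in advance, because covariate adjustment costs nothing visible when PS has no effect.

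Two further replies bear on the remedy. Four strata lose power when PS is weak, and at the interim (55 deaths) they would have averaged 55/4, about 14 deaths each. Both are good reasons to prefer a covariate to extra strata and to leave the interim alone. The sensitivity model in 2.1.3 does cover chance imbalance in PS, but it is optional and triggered by imbalance, whereas the efficiency gain depends on prognostic strength.

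**Conclusion.** This is a missed efficiency gain, not a defect in validity or in the event count. The organ-only test holds its level, follows the randomization factor, and has the stated 80% power for an overall HR of 0.67.

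If 0.67 holds within PS levels and PS is strongly prognostic (assumed HR 2.0 to 2.5, PS 1 in 30 to 50%), organ-only power is about 69 to 75% against about 78 to 80% with PS adjustment. At PS HR 1.5 or below the difference is about 0 to 1.5 points, which would not matter in practice. All of these sizes rest on assumed PS inputs and on the simulation settings above.

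**What to change.** In 2.1.1 and 2.1.2, before any final between-arm data are seen:

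- Pre-specify PS (0/1) as a covariate in the Cox model stratified by primary organ. Use its score test for the final OS comparison and its HR as the headline estimate.
- Do not use four organ × PS strata.
- Report the organ-only stratified log-rank test as a sensitivity analysis.
- Leave the completed interim test and its boundary as they are. Even with a different final statistic, the two stated levels sum to 0.0024 + 0.0992 = 0.1016, so the study-wise error cannot move materially.

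If between-arm results are already known, the primary test should not change; the PS-adjusted model can then only be a labelled supplementary analysis.

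The cost is SAP wording, with no extra patients or events. The small downside is that the HR becomes conditional on PS as well as organ, and the model assumes a proportional PS effect.

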#### **2.1.2. Analysis methods using statistical models**

As a treatment effect measure, hazard ratios and their confidence intervals for treatment effects between groups are estimated using stratified Cox proportional hazards models with the same factors as the stratified log-rank test for the primary analysis.

To investigate the interaction between treatment effect and the subpopulation, hazard ratios and their 95% confidence intervals for treatment effects will be calculated using unstratified Cox's proportional hazards model. These will be done in an exploratory manner with respect to the following factors. Because these analyses are not adequately powered and do not adjust for multiplicity, the results of each subgroup analysis should be interpreted as exploratory.

Factors planned for subgroup analysis:

- PS0/1
- Age 65 years or older/<
- Gender (male/female)
- Primary organ (gastrointestinal tract/hepatobiliary pancreas)
- Organ of origin (esophagus/stomach/small intestine/large intestine/pancreas/biliary tract/liver NEC (liver primary or liver metastasis of unknown primary))
- Organ of origin (pancreas/non-pancreas)
- Extent of extension of the primary lesion (locally advanced/distant metastasis or recurrence)
- Extent of extension of the primary lesion (locally advanced/distant metastasis/recurrence)
- Prior radical resection of the primary lesion (none/present)
- Pathological diagnosis was biopsy/resection specimen
- Grade 3 tumour with morphologically similar features of NETs but Grade 3 proliferative activity/morphologically more atypical (previously classified as poorly differentiated endocrine carcinoma) on histopathology with central pathology
- Histopathological examination by central pathological diagnosis, including Small cell carcinoma/Large cell carcinoma /
- Histopathologically diagnosed by central pathology, Ki67 50% or higher/less than 50%

### **2.1.3. Method of supplementary analysis**

To evaluate the robustness of the primary analysis results, the following sensitivity analyses will be performed if necessary.

- Hazard ratios and their confidence intervals for treatment effects between arms using a unstratified Cox proportional hazards model for all enrolled patients.
- Hazard ratios and their confidence intervals for treatment effects between arms using stratified Cox proportional hazards models with the same factors as the test of the primary analysis, with background factors biased between arms as covariates, for all enrolled patients.
- Hazard ratios and their confidence intervals for treatment effects between arms using the same stratified Cox proportional hazards model as in the primary analysis (\* analysis population is all eligible patients).
- Hazard ratios and their confidence intervals for treatment effects between arms using the same stratified Cox proportional hazards model as in the primary analysis (\* analysis population is patients eligible for central pathology review).

### **2.1.4. Handling of missing data**

No imputations will be made for missing data.

### **2.1.5. Summary of follow-up status**

For all enrolled patients, the follow-up period is calculated for each patient according to the following definitions, and the summary statistics (minimum, 25th percentile; median, 75th percentile; maximum) are calculated.

Follow-up time (days) = (date of death (died patient) or date of last survival confirmation (survivors))-date of registration + 1

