## **Supplemental note for the final analysis (2021/6)**

<Data sets for the analysis (see Section 5.2 in the SAP)>

Data sets based on a follow-up survey on March, 2021.

<Population for primary analysis (see Section 2 in the SAP)>

OS and PFS are analyzed for all enrolled 170 patients. As supportive analysis for OS and PFS, two analysis populations (all eligible 166 patients and 152 patients eligible for centrally pathological review) are also analyzed. Response rate is analyzed for 157 eligible patients with measurable disease.

<Population for safety analyses (see Section 3 in the SAP)>

Safety analyses are performed on 164 eligible and treated patients.

<Information time>

Among the 170 patients for the efficacy population, the total number of observed events was 55 at the timing of interim analysis and that is 151 in the final analysis. Thus, the information time, the calculated significance level, and boundary in the interim and final analyses are as follows.

- The interim analysis
  - Information time: 55/150 (0.36666666666666600)
  - Two-sided significance level:  $\alpha' = 0.0024177822594063$
  - Boundary for log-rank test statistic =  $\pm 3.0334456905510900$
- The final analysis
  - Information time: 1.00 (all the remaining alpha level is spent)
  - Two-sided significance level:  $\alpha' = 0.0992019861996200$
  - Boundary for log-rank test statistic =  $\pm 1.6487347573298200$

<Adjustment factors>

The primary analysis (stratified log-rank test) for overall survival is planned to use a randomization adjustment factor of primary organ (gastrointestinal vs. hepatobiliary-pancreatic). For a reason that the number of deaths is enough for each stratum in the adjustment factor, the stratified log-rank test uses the adjustment factor as planned.

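### The all-patient follow-up summary in SAP 2.1.5 mainly measures survival; a reverse Kaplan-Meier median should be the main follow-up summary

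*SAP*

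**What the plan says.** SAP section 2.1.5, on follow-up status, sets the population and the statistics: "For all enrolled patients, the follow-up period is calculated for each patient according to the following definitions, and the summary statistics" are the minimum, the 25th, 50th and 75th percentiles, and the maximum. The time itself is "Follow-up time (days) = (date of death (died patient) or date of last survival confirmation (survivors))-date of registration + 1". Deaths and survivors are pooled, and the percentiles take no account of which times ended in death.

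The Supplemental note for the final analysis analyses overall survival in all 170 enrolled patients and states that "the total number of observed events was 55 at the timing of interim analysis and that is 151 in the final analysis".

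The SAP as available gives no other follow-up measure: no reverse Kaplan-Meier median, no summary restricted to patients still alive, and no comparison with potential follow-up. Section 7 does anticipate some loss to follow-up, without giving a rate, and section 2.1.4 imputes nothing.

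**The concern.** The time in 2.1.5 is each patient's overall survival time with the event indicator removed. When most patients have died, its median follows mortality more than tracing. If survival improves, follow-up appears longer; if survival worsens, it appears shorter, even when patients are traced equally well.

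Readers use median follow-up to judge how long patients could have been observed and whether living patients were kept under observation. Here that question concerns the 170 − 151 = 19 patients without a recorded death: were they confirmed alive close to the March 2021 survey, or censored much earlier? A quartile summary dominated by 151 death times answers this badly. It could also make follow-up look shorter than the one year that section 7 plans after the last enrolment.

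**Working it through.** **Inputs from the SAP.** Section 7: "we assume a median survival of 8 and 12 months (HR=0.67) for inferior and superior treatment groups"; 6 years of enrolment plus 1 year of follow-up; "Planned enrollment: 85 patients in each group and 170 patients in both groups". Supplemental note for the final analysis: 170 patients, 151 deaths.

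**Assumptions, not in the SAP.** Exponential survival, uniform accrual over 72 months, and exponential loss to follow-up at 0% to 30% per year.

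**Reproducing the plan's own figure.** Required events by Schoenfeld's formula are 4(z₀.₉₅ + z_power)² / (ln HR)², with HR = 8/12.
- 80% power: 4 × (1.645 + 0.842)² / 0.1644 = 150.4 (SAP: 150).
- 70% power: 4 × (1.645 + 0.524)² / 0.1644 = 114.5 (SAP: 114).

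Both agree up to rounding, so the planning medians are being read as intended.

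**Step 1: share of survival times.** 151/170 = 88.8%. At most 19/170 = 11.2% of the times can be censoring times.

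**Step 2: pooled median survival.** Solve 0.5 × (2^(−t/8) + 2^(−t/12)) = 0.5. At t = 9.74 the bracket is 0.430 + 0.570 = 1.000, so t is about 9.7 months.

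**Step 3: the 2.1.5 median with complete follow-up.** Every patient then has at least 12 months' potential follow-up. Below 12 months, observed time and survival time have the same distribution. Since 9.7 < 12, the 2.1.5 median equals the pooled survival median, apart from sampling error. It also falls below the 12-month minimum, purely because patients died.

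**Step 4: median potential follow-up.** Uniform accrual gives 12 + 72/2 = 48 months. The 2.1.5 median is about 9.7/48 = one fifth of that.

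**Step 5: response to loss to follow-up.** Simulation of 1,000 trials of 170 patients per setting; average medians in months:

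| Survival medians | Loss per year | 2.1.5 median | KM median OS | Reverse KM follow-up | Median in patients not known dead | Deaths |
|---|---|---|---|---|---|---|
| 8 / 12 | 0% | 9.8 | 9.85 | 48.6 | 22.9 | 155 |
| 8 / 12 | 5% | 9.2 | 9.8 | 42.3 | 17.6 | 148 |
| 8 / 12 | 10% | 8.7 | 9.8 | 36.2 | 14.5 | 140 |
| 8 / 12 | 30% | 6.9 | 9.8 | 20.1 | 8.0 | 115 |
| 9 / 13.5 | 0% | 10.95 | 11.1 | 49.5 | 23.8 | 152 |
| 9 / 13.5 | 10% | 9.6 | 11.0 | 36.4 | 15.6 | 137 |

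At 8/12 months, 10% loss per year lowers the 2.1.5 median by 9.77 − 8.69 = 1.1 months and the reverse Kaplan-Meier median by 48.55 − 36.21 = 12.3 months.

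**Step 6: confounding with survival.** The section 7 table also considers 7.0 vs. 10.5 and 9.0 vs. 13.5 months.
- Complete follow-up at 7.0/10.5 gives 9.74 × 7/8 = 8.5 months, about the same as 8/12 with 10% loss per year (8.7).
- Medians of 9/13.5 with 10% loss per year give 9.6, about the same as 8/12 with none (9.8). The reverse Kaplan-Meier medians for that second pair are 36.4 and 48.6, so that measure separates them.

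**The case against.** The strongest reply is that the figure is correctly computed as defined, that observed time on study is a legitimate description, and that nothing depends on it. It feeds no test, boundary or analysis trigger. Maturity in this SAP is governed by events, and 151 were observed against 150 required. All of that stands and limits the point to reporting.

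A reader might infer that the 2.1.5 median is identical to median survival and carries no information on completeness. The document does not support that. The near-equality needs little loss: at an assumed 30% per year the median drops to 6.9 months while Kaplan-Meier median survival stays near 9.8. Section 2.1.1 already requires the Kaplan-Meier median, so a wide gap between the two would be a warning. It would still be only an indirect signal, and would not say how long patients were followed. With heavier administrative censoring the two also separate without any loss: in an interim-like setting (86 patients, about 51 deaths) the 2.1.5 median is about 6.5 months against 9.8 for survival.

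A reader might also infer that early censoring among the 19 would be wholly concealed, or that follow-up was in fact poor. Neither follows. The planned survival curves and Greenwood intervals reflect censoring, and only 19 patients are unresolved. The count of 151 deaths fits 9/13.5 months with complete follow-up (about 152) as well as 8/12 months with loss between 0% and 5% per year (155 and 148), so it does not settle completeness either way.

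Finally, the SAP is an abridged translation and its protocol is not at hand, so another follow-up summary may exist elsewhere. The definition in 2.1.5 is nonetheless fixed as written.

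**Conclusion.** The point holds as a reporting weakness. With 151 of 170 patients dead, the 2.1.5 median mainly reflects survival: about 9.7 months under the planning medians with little loss, against about 48 months' median potential follow-up. It reacts modestly to loss (about 1.1 months at 10% per year), and a change of that size cannot be told apart from a change in prognosis within the range section 7 itself considers.

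These sizes rest on exponential survival, uniform 6-year accrual plus 1 year, and assumed loss rates. The 89% share of death times rests on the SAP's own counts alone. The primary log-rank test, its alpha and its power are unaffected.

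**What to change.** Amend section 2.1.5 as follows:

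- Make the reverse Kaplan-Meier median follow-up (deaths censored at date of death) the main follow-up summary, overall and by arm.
- Add minimum, quartiles and maximum of time from registration to last survival confirmation among patients not known to have died. State that this subset favours recently enrolled patients: with no loss its simulated median is 22.9 months against 48.6 by reverse Kaplan-Meier, so it supplements the main measure and does not replace it.
- The existing all-patient summary need not be dropped; label it as observed time on study.

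The cost is one paragraph and a few lines of code. The dates are those already needed for overall survival, so no new data are required.
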